### Confidentiality {27}

Study participants will provide explicit consent to the use of identifiable data for the purposes of the conduct of the study. Personal identifiable data (PID) will be stored separately from anonymised study data on a secure server hosted within the University of Cambridge School of Clinical Medicine Secure Research Computing Platform. PID will be accessible to the SIMPLIFIED trial team within the Cambridge Clinical Trials Unit, monitors, auditors and inspectors as required. It is necessary to (1) perform validation of NHS/CHI numbers and linkage to routinely collected datasets (NHS England, SAIL, eDRIS) and (2) to generate datasets with participant details for mail merge creation of questionnaires and is therefore imperative to the conduct of the study.

### Plans for collection, laboratory evaluation and storage of biological specimens for genetic or molecular analysis in this trial/future use {33}

Laboratory data will be obtained from the results of routinely collected blood tests via the UKRR on an on-going basis. Calcium and phosphate concentrations are measured regularly in all UK dialysis patients as part of standard care, and these data are already submitted to the UKRR. These results will be linked daily from the UKRR to the SIMPLIFIED secure data hosting area on all participants in the trial. Monitoring for hypercalcaemia will be driven by routine clinical practice and management based on local hypercalcaemia guidelines and practices.

## Statistical methods

### Statistical methods for primary and secondary outcomes {20a}

#### Primary outcome analysis

The primary efficacy analysis will be by intention-to-treat comparing patients randomised to cholecalciferol and those randomised to receive standard of care, adjusted for baseline characteristics including age, gender, diabetic status and length of time on dialysis. SIMPLIFIED is an event-driven trial and will continue until 2200 events (deaths) have occurred. Prior to the primary analysis, survival status will be confirmed by cross-referencing UKRR and ONS data. For participants where no death has been recorded by either ONS or the UKRR at the end of the trial, follow-up time will be censored at the point of last known follow-up. Last known follow-up will be defined as whichever is most recent of either the date of last recorded UKRR-submitted dialysis results or last 6-monthly questionnaire follow-up. The primary analysis will be carried out after the occurrence of 2200 events, using Cox proportional hazards regression modelling to test the effects of randomisation to cholecalciferol on all-cause mortality. The survival times will be summarised using Kaplan–Meier curves. All estimates of hazard ratios associated with treatment and baseline covariates will be provided with 95% confidence intervals and *p* values.

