**Fig. 2 Fig2:**
[figure not shown]
Suspected vitamin D toxicity. If all identifiable causes of hypercalcaemia (Fig. 1) have been excluded or addressed, vitamin D toxicity should be considered in patients receiving cholecalciferol. This includes discontinuation of 1α-hydroxylated vitamin D compounds, since toxicity results from increased circulating calcitriol concentrations. Therefore, vitamin D toxicity cannot be attributed to cholecalciferol in the presence of concomitant treatment with 1α-hydroxylated compounds

Participants may withdraw consent for continuation in the trial at any point. Withdrawal will constitute discontinuation of the trial drug for those in the cholecalciferol arm. In the event that a participant withdraws from the trial, ongoing data capture through linkage will continue unless the participant also withdraws from data linkage and any future data capture.

Trial participants who receive a kidney transplant or become pregnant should be withdrawn from cholecalciferol if in that group; however, they will remain within the trial providing ongoing data captured through linkage unless the participant withdraws from data linkage.

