**Fig. 3 Fig3:**
[figure not shown]
Assessment schedule. *Eq5D data collection ceased in April 2023. QoL, quality of life; SAR, serious adverse reaction; SUSAR, suspected unexpected serious adverse event; HES, Hospital Episode Statistics; ONS, Office of National Statistics; UKKR, UK Renal Registry; SAIL, Secure Anonymised Information Linkage; eDRIS, Electronic Data Research and Innovation Service

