### Sample size {14}

The SIMPLIFIED study is an event-driven trial. It is estimated that the control arm has a 3-year survival of 68% [1]. It is estimated that randomisation of 4200 patients would yield 2200 primary outcome events (deaths) over 7–8.5 years, resulting in 90% power at 5% significance (two-sided) assuming a hazard ratio of 0.87. Dropout is assumed to be negligible given the national death registry data source for primary endpoint collection.

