### Methods in analysis to handle protocol non-adherence and any statistical methods to handle missing data {20c}

The primary efficacy analysis will be conducted on the intention-to-treat (ITT) population, defined as all randomised participants, analysed according to their original treatment allocation, regardless of treatment adherence or post-randomisation events. For the primary endpoint (all-cause mortality), missing data are expected to be rare, as vital status will be ascertained for virtually all participants via routine data linkage and follow-up.

Further details in handling missing data are included in the statistical analysis plan which will be included as an appendix in the publication of the results manuscript. Further detail on the CEA and CUA will be detailed within the Health Economic Analysis Plan (HEAP).

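### Survivors are censored at their last dialysis result or questionnaire while deaths are counted to the end of the trial, which pushes the survival curves down; the primary hazard ratio is affected only if loss of contact differs by arm

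*Protocol article*

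**What the plan says.** The rule is stated twice in the Protocol article, in *Data management {19}* and in *Primary outcome analysis* under {20a}. Survival status is cross-checked between ONS and the UKRR. If neither source shows a death by the end of the trial, the participant is censored at "whichever is most recent of either the date of last recorded UKRR-submitted dialysis results or last 6-monthly questionnaire follow-up".

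Other sections bear on this rule:

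- *Sample size {14}*: "Dropout is assumed to be negligible given the national death registry data source for primary endpoint collection".
- *Methods in analysis to handle protocol non-adherence … {20c}*: "vital status will be ascertained for virtually all participants via routine data linkage and follow-up". The same section defines an intention-to-treat population that disregards events after randomisation.
- *Criteria for discontinuing or modifying allocated interventions {11b}*, on participants who are transplanted or become pregnant: "they will remain within the trial providing ongoing data captured through linkage unless the participant withdraws from data linkage".
- Note to Fig. 3 under *Participant timeline {13}*: "Eq5D data collection ceased in April 2023". *Trial status* has follow-up running to the end of Q4 2025.

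**The concern.** Deaths and survivors' follow-up time come from different systems. A death is taken from national registration, whether or not the participant was still sending dialysis results. The time at risk of someone who has not died ends at the last trace in the dialysis or questionnaire data. Take a participant who leaves the dialysis-results stream at year 2. If they die at year 5 they contribute one death and five years at risk; if they are alive at year 5 they contribute two years. Whether years 2 to 5 count is decided by the outcome.

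The participants affected are those who leave the stream alive. Transplant is the clearest route, because dialysis results would be expected to stop while {11b} keeps the person in the trial through linkage. Since April 2023 the questionnaire has not been available as a second source of contact, so for roughly the last 2.7 years of follow-up (April 2023 to December 2025) the censoring date can be extended only by dialysis results.

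At stake are the Kaplan-Meier curves that the article plans to report, the absolute survival differences read from them, and any life-years figure built on them. The primary hazard ratio is at stake only if the rate of leaving differs between arms.

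**Working it through.** **The plan's own figure.** *Sample size {14}* says "randomisation of 4200 patients would yield 2200 primary outcome events (deaths) over 7–8.5 years". The stated power is 90% for a hazard ratio of 0.87 at a two-sided 5% level. By Schoenfeld's formula with 1:1 allocation, deaths = 4(1.960 + 1.282)² / (ln 0.87)² = 4 × 10.51 / 0.01939 ≈ 2168. Freedman's formula gives 2175. Power at 2200 deaths is 90.4%. The figure reproduces, and the censoring rule does not alter it.

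**Inputs from the article.** 4200 patients, 1:1; control 3-year survival 68%, so a constant hazard of −ln(0.68)/3 = 0.1286 per year and 5-year survival of exp(−5 × 0.1286) = 52.6%; tests at least monthly while on dialysis (*Adverse event reporting and harms {22}*).

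**Assumed, not in the article.** The yearly rate of leaving the dialysis-results stream alive, and mortality afterwards.

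**Survival curves.** Simulation with 5-year uniform accrual, 8.5 years in total, and mortality unchanged after leaving. The column headed common date censors every survivor at one cut-off; the column headed rule applies the article's text. Control arm:

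| Leaving per year | 3-year, common date | 3-year, rule | 5-year, common date | 5-year, rule | 5-year gap (points) |
|---|---|---|---|---|---|
| 0% | 0.681 | 0.681 | 0.527 | 0.526 | 0.1 |
| 3% | 0.680 | 0.673 | 0.525 | 0.506 | 1.9 |
| 6% | 0.680 | 0.665 | 0.525 | 0.488 | 3.7 |
| 10% | 0.680 | 0.656 | 0.525 | 0.463 | 6.2 |

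The 0% row is the case of participants who stay on dialysis. If mortality after leaving is lower (30% of the on-dialysis hazard, assumed), the 5-year gaps grow to 2.7, 5.1 and 8.3 points (0.545 vs 0.518, 0.563 vs 0.512, 0.585 vs 0.502).

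**Hazard ratio, equal leaving.** In the same simulation a true 1.00 stays at 1.00. With a true 0.87 the common date gives 0.870 and the rule 0.872, 0.874 and 0.876 at 3%, 6% and 10% per year.

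**Hazard ratio, unequal leaving.** Here the set-up is 5% per year transplanted in both arms with post-transplant death at 3% per year, accrual over 8.55 of 8.8 years, and further loss of contact that differs by arm (all rates assumed). The true hazard ratio is 1.00. SE = 2/√2200 = 0.0426. Type I error = Φ(−1.96 + δ) + Φ(−1.96 − δ), with δ = |ln HR|/SE.

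| Further loss per year, control vs cholecalciferol | HR under rule | δ | Two-sided type I error |
|---|---|---|---|
| 2% vs 1% | about 0.985 | 0.0151/0.0426 = 0.35 | about 6.5% |
| 4% vs 2% | about 0.965 | 0.0356/0.0426 = 0.84 | about 13% |

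With the 4% vs 2% imbalance reversed, the hazard ratio moves to about 1.04.

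**The case against.** The strongest reply is that the primary result is a Cox hazard ratio, and nothing in the article suggests that loss of dialysis results differs by arm. UKRR data come from routine care and not from trial contact, flow for all participants, and are linked daily (section {33}). People who opted out of the UKRR are excluded at entry. Stopping the drug is not withdrawal, and linkage continues even after withdrawal unless it is refused. The questionnaire, the route most open to arm-related dropout, ended for everyone in April 2023. This stands, and it limits the point to the survival curves and absolute measures unless an imbalance is found.

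A second reply is that censoring at the date last known alive protects against treating unlinked or emigrated people as survivors. This stands in part. It justifies the rule for participants who cannot be linked, but not for the large majority who can.

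A third is that the magnitudes rest on assumed rates. They do. In particular, the set-up used for the unequal-leaving table applies 68% to the on-dialysis hazard only, so its cohort has about 69.7% survival at 3 years, not the 68% the article gives for the control arm.

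Two stronger readings should be resisted. A reader might infer that {14} and {20c} contradict the rule. They do not: they speak of capturing deaths and of rare missing vital status, and neither sets a censoring date. They show only that the early censoring is avoidable. A reader might also infer that, late in follow-up, only people destined to die remain at risk. That is wrong, because everyone still in contact stays in the risk set; only its out-of-contact members are selected on outcome.

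**Conclusion.** The concern holds for survival curves and absolute measures. The rule is fixed in the protocol text, so it is not a detail left open for the SAP. It makes survivors' follow-up depend on contact while deaths do not. Kaplan-Meier survival is biased downward by about 0.7 to 2.4 points at 3 years and about 2 to 6 points at 5 years, if 3–10% per year leave the dialysis-results stream and their mortality is unchanged. The bias is about 0.1 point or less for participants still on dialysis. Between-arm differences in survival, and life-years derived from these curves, inherit the distortion; how far the economic analysis uses them is left to the Health Economic Analysis Plan.

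A reader might infer that the primary test has a 13% type I error. The documents do not support that. The figure needs an assumed 4% vs 2% yearly difference in loss between arms; at 2% vs 1% it is about 6.5%, and with equal loss the hazard ratio is almost unbiased. Unequal loss is possible in an open-label trial but is not shown.

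Severity: should-fix. Confidence is high that the rule is as described and that it lowers the curves whenever some participants leave alive. It is lower for the size, because the article gives no leaving rates.

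**What to change.** Amend both *Data management {19}* and *Primary outcome analysis*, and carry the change into the SAP:

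1. Censor every linked participant without a registered death at one common date to which ONS and devolved-nation death registration is complete, and count deaths only up to that date.
2. Censor earlier only at withdrawal from data linkage, or at emigration where this is known.
3. Use the last UKRR result or questionnaire date only for participants who cannot be linked.
4. Keep the present rule as a sensitivity analysis.

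The cost is wording, and the event target is unchanged. The change can be made before the analysis planned for Q2 2026. There is a small downside: the article names no source for emigration, so undetected emigrants would be treated as alive to the cut-off. The sensitivity analysis covers that.

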#### Secondary outcome analyses

Secondary assessments will evaluate the effect of cholecalciferol on quality of life using EQ-5D-5L data. Intention-to-treat analyses on the effect of randomisation to cholecalciferol on infections requiring admission, incidence of malignancy, fracture requiring admission and hospitalisation with cardiovascular events including atherosclerotic events, arrhythmias, heart failure and stroke will be carried out. Analysis of the time to first non-atherosclerotic cardiovascular event will be assessed.

Relevant secondary endpoints will be assessed using time to event analysis (Cox proportional hazards regression modelling). Time to event data will be summarised using Kaplan–Meier curves. Events that may occur multiple times (acute coronary syndrome, fracture) will be analysed using repeated events analysis. The treatment effect for secondary endpoints will be reported using point estimates, with nominal 95% confidence intervals and *p* values.

Cost-effectiveness will be gauged using a cost-effectiveness analysis (CEA) and cost-utility analysis (CUA). For both, the costing perspective will be that of the NHS (specifically that of secondary care—restricted to this perspective as resource data is only collected from Hospital Episode Statistics (HES) and related sources). In the CEA, outcomes will be compared in terms of life years gained (related to the primary outcome). For the CUA, outcomes will be compared using quality adjusted life years, calculated from EQ-5D-5L. For both analyses, a range of time frames (time horizons) will be considered, starting from a year and then at subsequent years for the range available within the data.

The overall conclusions of the study in terms of formal inference to reject or retain the null hypotheses associated with each endpoint will explicitly account for multiple testing to restrict the family-wise error rate (the overall chance of one or more type I errors) to below 5%.

### Interim analyses {21b}

A feasibility assessment will be carried out between months 12 and 15 of the trial. Feasibility will be predicated on recruitment rate (target 887 patients recruited after 12 months), and separation between arms by plasma vitamin D concentration after 4 months of treatment of 20 nmol/l.

### Methods for additional analyses (e.g. subgroup analyses) {20b}

Details will be documented in the statistical analysis plan which will be published as an appendix in the main results manuscript.

### Methods in analysis to handle protocol non-adherence and any statistical methods to handle missing data {20c}

The primary efficacy analysis will be conducted on the intention-to-treat (ITT) population, defined as all randomised participants, analysed according to their original treatment allocation, regardless of treatment adherence or post-randomisation events. For the primary endpoint (all-cause mortality), missing data are expected to be rare, as vital status will be ascertained for virtually all participants via routine data linkage and follow-up.

Further details in handling missing data are included in the statistical analysis plan which will be included as an appendix in the publication of the results manuscript. Further detail on the CEA and CUA will be detailed within the Health Economic Analysis Plan (HEAP).

### Plans to give access to the full protocol, participant-level data and statistical code {31c}

The full protocol is available on the study website and is submitted as supplementary material with this manuscript. De-identified participant data and statistical code will be shared on reasonable request to the corresponding author.

## Oversight and monitoring

### Composition of the coordinating centre and trial steering committee {5d}

#### Trial Management Group (TMG)

The TMG will meet at least weekly during initial set up, and then regularly as required to oversee the running of the trial. TMG members will include chief investigator, co-investigators, trial statistician(s), trial coordinator(s) and data manager(s) at the Cambridge Clinical Trials Unit (CCTU).

#### Trial Steering Committee (TSC)

The TSC is responsible for the review of the trial and related activities at regular intervals. The TSC also provides overall supervision for the trial, to ensure that it is conducted in accordance with the protocol and GCP and to provide advice through its independent chairman. The committee will aim to convene at regular intervals to review the data and discuss the recommendations from the IDMC. The details of the TSC are set out in the SIMPLIFIED Trial Steering Committee Charter, the composition of which will be approved by the NIHR.

### Composition of the data monitoring committee, its role and reporting structure {21a}

The Independent Data Monitoring Committee (IDMC) comprises an unblinded independent group, as defined in the SIMPLIFIED Data Monitoring Committee Charter document, which will define the role of the IDMC. The IDMC will have access to unblinded treatment allocation data, which it will use to review accumulating safety and efficacy data. The IDMC will meet regularly throughout the trial—from trial opening to final follow-up—and will make recommendations to the Trial Steering Committee regarding continuation, modification or termination of the trial.

### Adverse event reporting and harms {22}

This trial is categorised by the Medicines and Healthcare products Regulatory Agency as a type A study (no higher than the risk of standard medical care). Patients are followed up regularly at their local dialysis units throughout this study, and an ongoing evaluation of risk will continue throughout the recruitment period.

Serious adverse events (SAEs) will not be recorded and reported within the usual 24-h time period but will instead be captured using the routine data sources. SAE line listings will be periodically generated and reviewed by the chief investigator and reported to the sponsor. Serious adverse reactions or suspected unexpected reactions that are directly attributable to cholecalciferol will require reporting by site teams to the SIMPLIFIED trial office within 24 h of awareness.

Dialysis patients are intensively monitored as part of standard care with comprehensive biochemical and haematological tests being performed at least monthly. All dialysis data for each patient are reviewed by renal unit staff, typically in “sit down ward round” meetings, where clinical parameters and test results are reviewed and treatments adjusted. This approach will allow rapid detection of elevated calcium levels which is a potential concern with the administration of high-dose cholecalciferol, and clear guidance is provided to sites should hypercalcaemia occur via the hypercalcaemia (Fig. 1) and vitamin D toxicity (Fig. 2) algorithms.

### Frequency and plans for auditing trial conduct {23}

The sponsor will complete risk-based and targeted onsite and remote monitoring of trial sites based on the trial risk assessment, patient safety and regulatory compliance. No formal regulatory or registry audits are planned, but should a monitoring visit or audit be requested, the trial team will make the required trial documentation and source data available to the auditor’s representative.

### Plans for communicating important protocol amendments to relevant parties (e.g. trial participants, ethical committees) {25}

Protocol amendments must be reviewed and agreement received from the sponsor for all proposed amendments prior to submission to the Research Ethics Committee (REC) and/or Medicines Health and Regulatory Authority (MHRA). The only circumstance in which an amendment may be initiated prior to REC and/or MHRA approval is where the change is necessary to eliminate apparent, immediate risks to the participants (Urgent Safety Measures). In this case, accrual of new participants will be halted until the REC and/or MHRA approval has been obtained. All correspondence with the REC will be retained in the Trial Master File/Investigator Site File. All REC/HRA/MHRA approvals will be shared with trial sites for local C&C approvals (as required) prior to trial site implementation. A complete list of all protocol amendments will be included in the final clinical study report.

### Dissemination plans {31a}

On completion of the trial, the data will be analysed and tabulated and a Final Study Report prepared. The results of this trial may be presented at scientific meetings and will subsequently be published in peer review journals. The NIHR Health Technology Assessment (HTA) requires notification of all outputs arising from the trial 28 days before publication. Results will be shared with participants in an accessible format.

## Discussion

Dialysis is a life-sustaining treatment, but there is a major unmet need to improve survival; one third of patients have died within 3 years of commencing renal replacement therapy, an outcome that is worse than most common cancers. Many interventions are employed in dialysis, aiming to improve patients’ survival and quality of life, but with little supporting evidence. Vitamin D deficiency is observed in the majority of patients on dialysis, and there is strong epidemiological evidence that low levels of vitamin D are associated with increased risk of all-cause mortality, cancer, cardiovascular events and infection. However, the impact of population-wide vitamin D replacement on dialysis outcomes is unknown.

Building on the lessons learned from the design and conduct of earlier trials using routinely collected electronic health care data to capture outcomes, the SIMPLIFIED trial has a pragmatic study design to address the key question of whether high-dose cholecalciferol improves survival in patients on dialysis [21]. The study was designed to place minimal burden on patients and dialysis unit staff and to utilise routinely collected data and centralised data collection to report endpoints wherever possible. Consequently, there were no specific study visits after the initial baseline visit, which enabled the trial to continue throughout the COVID-19 pandemic when most studies had to pause due to diversion of resources.

Patients receiving dialysis are intensively supervised as part of routine care and have frequent routine blood monitoring which automatically flows to the UKRR primarily for audit purposes. This established infrastructure means that employing methods to harness routinely collected data in clinical trials is ideally suited to this patient population. By harnessing the efficiencies of using data from such sources, with the available budget, it is feasible to enrol a large number of patients receiving dialysis into this study and follow for several years to definitively answer the question of whether high-dose cholecalciferol improves survival for patient on dialysis. Cholecalciferol is a low-cost and easy to administer intervention, and should it show benefit, then these findings should be readily translatable to dialysis patients more broadly both in the UK and beyond.

It is anticipated that the SIMPLIFIED trial will pave the way for future registry trials in the UK as it will serve as a vehicle to develop the infrastructure and experience needed to support more complex trials using this approach. In addition, since all relevant data will continue to be routinely captured on all participants beyond the end of the follow-up period, it offers a very cost-effective approach for extended follow-up and evaluation of long-term outcomes of participants.

